## Summary of Changes from the Previous Version:

| Affected Section(s)              | Summary of Revisions Made                                                                                                  | Rationale                                                                                                                                                                                                                                                          |
|----------------------------------|----------------------------------------------------------------------------------------------------------------------------|--------------------------------------------------------------------------------------------------------------------------------------------------------------------------------------------------------------------------------------------------------------------|
| Title page & all page headers    | Previous approved version: 2020 March 02
Current version date: 2022 November 2022
Addition of a version number: 4.0  | To reflect changes to document and more accurately track protocol version.

V1.0 – 03 February 2019

V2.0 – 14 March 2020

V3.0 – 02 March 2020

V4.0 – 25 November 2022                                                                   |
| Various                          | Grammatical and typographical                                                                                              | Fix any grammatical and typographical issues                                                                                                                                                                                                                       |
| 6.1.1
6.2.1
6.2.2
6.2.4 | Minor changes to include both Zofran® and the generic ondansetron oral solution as options for the interventional product. | Due to intermittent availability of the brand name interventional product, Zofran®, the protocol will now allow for the use of both generic oral ondansetron and Novartis brand Zofran®. Use is based on availability of the primary product, Zofran®. The generic |

|      |                                                                                                 |                                                                                                                                                                                |
|------|-------------------------------------------------------------------------------------------------|--------------------------------------------------------------------------------------------------------------------------------------------------------------------------------|
|      | Addition of a second placebo formulation to match the smell of the generic ondansetron product. | ondansetron oral solution can be used if Zofran® is not available.                                                                                                             |
| 10.4 | Update to Protocol Change Amendment Table                                                       | Summary of changes made to the study protocol: Inclusion of the generic oral ondansetron product and matching placebo formulation.                                             |
| 12   | Inclusion of additional appendices. Now included are Appendices A, B, C, and D.                 | Inclusion of JAMP Pharmaceuticals generic Ondansetron Oral Solution Product Monograph.

Inclusion of the generic ondansetron oral solution matching placebo formulation. |

## STATEMENT OF COMPLIANCE

The trial will be conducted in accordance with Good Clinical Practice (GCP) as described in Health Canada's section C.05.010/Division 5 of the Food and Drug Regulations, International Conference on Harmonisation-Good Clinical Practice (ICH-GCP E11 and ICH-GCP E6 R2), Tri-Council Policy Statement (TCPS2, 2018); applicable federal, provincial and local regulatory and legislative requirements and in compliance with the Terms and Conditions of the CIHR SPOR Award. The Principal Investigator will assure that no deviation from, or changes to the protocol will take place without prior documented authorization/approval from a duly constituted Research Ethics Board (REB), except where necessary to eliminate an immediate hazard(s) to the trial participants. All personnel involved in the conduct of this study have completed Human Subjects Protection and ICH-GCP Training.

The protocol, informed consent form(s), recruitment materials, and all participant materials will be submitted to the REB for review and approval. Approval of both the protocol and the consent form must be obtained before any participant is enrolled. Any amendment to the protocol will require review and approval by the REB before the changes are implemented to the study. All changes to the consent form will be REB approved and a determination will be made regarding whether a new consent needs to be obtained from active participants who provided consent using a previous approved version of the consent form.

A Health Canada Clinical Trial Application (CTA) for this study will not be submitted as per written waiver provided by a Health Canada representative during the pre-CTA consultation phase (*email correspondence dated 18 December 2017*).

## 1 PROTOCOL SUMMARY

### 1.1 SYNOPSIS

|                            |                                                                                                                                                                                                                                                                                                                                                                                                      |
|----------------------------|------------------------------------------------------------------------------------------------------------------------------------------------------------------------------------------------------------------------------------------------------------------------------------------------------------------------------------------------------------------------------------------------------|
| Title:              | MULTI-DOSE ORAL ONDANSETRON FOR PEDIATRIC GASTROENTERITIS: A RANDOMIZED CONTROLLED TRIAL                                                                                                                                                                                                                                                                                                             |
| Sponsor             | The University of Calgary                                                                                                                                                                                                                                                                                                                                                                            |
| Lead Investigator   | [name]                                                                                                                                                                                                                                                                                                                                                                                 |
| Study Description : | 
A phase III, double-blind, parallel-design, randomized, placebo controlled trial to compare multi-dose oral Ondansetron with placebo as treatment for vomiting secondary to acute gastroenteritis (AGE), after Emergency Department discharge.
 
The primary outcome will be the post-index visit Modified Vesikari Scale (MVS) score.
                                                   |
| Objectives:         | 
Primary Objective: To determine if in previously healthy children, who present to an ED with gastroenteritis associated vomiting, is the proportion who develop moderate to severe disease [Modified Vesikari Score (MVS) <math>\geq 9</math>] following ED evaluation, significantly different in those who receive ondansetron at home compared to those who receive placebo.
 |

|                                                                |                                                                                                                                                                                                                                                                                                                                                                                                                                                                                                                                                                                                                                                                                                                                                                                                                                       |
|----------------------------------------------------------------|---------------------------------------------------------------------------------------------------------------------------------------------------------------------------------------------------------------------------------------------------------------------------------------------------------------------------------------------------------------------------------------------------------------------------------------------------------------------------------------------------------------------------------------------------------------------------------------------------------------------------------------------------------------------------------------------------------------------------------------------------------------------------------------------------------------------------------------|
|                                                                | 
Secondary Objectives: In this group of patients, amongst those receiving active treatment versus placebo:
 
 
1. Is there a difference in the (a) duration of vomiting, (b) frequency of vomiting, or (c) the proportion who experience vomiting following ED disposition?
 
2. Is there a difference in the proportion who require an unscheduled health care provider visit?
 
3. Is there a difference in the proportion who require intravenous rehydration?
 
4. Is there a difference in the caregiver satisfaction with the therapy provided?
 
                                                                                                                                                       |
| Endpoints:                                              | 
Primary Endpoint: Post-index visit MVS score.
 
Secondary Endpoints will include:
 
 
1. Vomiting: Frequency, Duration, Proportion (i.e. yes/no)
 
2. Health care use: Emergency Department, Primary Care
 
3. Intravenous rehydration
 
4. Caregiver Satisfaction with Therapy Provided: Likert Scale
 
                                                                                                                                                                                                                                                                                                                                                                                                                                   |
| Study Population:                                       | Children and youth, age 6 months to 17.99 years will be enrolled at six (6) Canadian Emergency Departments. The total number of participants recruited will be 1030.                                                                                                                                                                                                                                                                                                                                                                                                                                                                                                                                                                                                                                                                  |
| Phase:                                                  | Phase III                                                                                                                                                                                                                                                                                                                                                                                                                                                                                                                                                                                                                                                                                                                                                                                                                             |
| Description of Sites/Facilities Enrolling Participants: | Participants will be enrolled at six (6) pediatric emergency departments across Canada: Alberta Children’s Hospital (Calgary, AB), Centre Hospitalier Universitaire de Sainte Justine (Montréal, QC), Children’s Hospital of Eastern Ontario (Ottawa, ON), London Health Sciences Centre – Children’s Hospital (London, ON), Stollery Children’s Hospital (Edmonton, AB), and the Health Sciences Centre – Children’s Hospital (Winnipeg, MB)                                                                                                                                                                                                                                                                                                                                                                                         |
| Description of Study Intervention:                      | Children who are provided a minimum of one dose of ondansetron as part of their routine clinical care AND meet other eligibility criteria will be randomized to receive an at-home kit with six (6) doses of Ondansetron Hydrochloride Dihydrate Oral Solution (4mg/5mL solution; dosed at 0.15mg/kg to a maximum single dose of 8mg) or equivalent volume in a Placebo Oral Solution to be administered no sooner than 8 hours after the initial clinical dose was provided by the ED physician. Over the subsequent 48 hours, the study intervention will be administered at a rate of 1 dose every 8 hours (q8h) to a maximum of 3 doses a day (in a 24 hour period (TID)) at the caregiver’s discretion . Two (2) additional doses will be provided to the caregiver in case the child vomits a dose. |
| Study Duration:                                         | Approximately 36 months of active recruiting will be required to meet the sample size of 1030.                                                                                                                                                                                                                                                                                                                                                                                                                                                                                                                                                                                                                                                                                                                                        |
| Participant Duration:                                   | Screening, consent, and randomization will take place at the initial ED (baseline) visit. The follow-up period will last 7 days with questionnaires issued 24 hours, 48 hours and 168 hours (7 days) after informed consent is received, by telephone or email.                                                                                                                                                                                                                                                                                                                                                                                                                                                                                                                                                                       |

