a First dose of study intervention can be administered 8 hours after administration of clinical dose of Ondansetron (at presenting ED visit)  
b Dose of study intervention will be administered at home based on caregiver determination. The final dose should be administered within 48 hours of first clinical dose of Ondansetron. Should the caregiver administer doses of study medication >72 hours post clinical dose of Ondansetron, it will be considered a protocol deviation. We will collect dose details at each follow-up time point. Any doses administered after the 48 hour follow-up time point will be recorded on the 168 hour (Day 7) follow-up questionnaire.

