## 4.3 JUSTIFICATION FOR DOSE

A standardized dose of 0.15mg/kg of oral ondansetron solution will be used in this study. The maximum singular dose of oral ondansetron provided will be 8mg, and the dose to be administered will be based on the weight of the participant at time of study enrollment. Enough study medication will be provided to enable the administration of a maximum of 6 doses at home. This dosing regimen has been shown to be effective, safe and is within the dosing range (0.13-0.26 mg/kg) that has previously been used for this indication.

A single dose of 8mg has been demonstrated to have a minimal effect on the QTc – prolonging it by only 0.4 msec. Moreover, within the recommended/commonly used dose range of 0.13-0.26 mg/kg, higher doses of ondansetron have not been found to be superior to lower doses.

Children will be administered oral medications as this route has proven to be effective, safe, pragmatic, and easy to use in young children.

Eligible children will receive up to 6 doses of medication [ondansetron oral solution (0.15 mg/kg/dose) or placebo] to be administered every 8 hours at the caregiver's discretion. Such caregiver-driven, after ED discharge dosing protocols are increasingly common with a recent description of a cohort of 996 children among whom 76% received ondansetron in the ED, and 71% were discharged with prescriptions for ondansetron. Moreover the median number of home doses of ondansetron prescribed was 10 (IQR: 6, 12). In this cohort, 7-day ED return rates were similar between groups (6% with prescription, 5% without, P = 0.66). We will have a standardized written handout that the research staff will employ explaining when we suggest that the medication be given.

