## 5 STUDY POPULATION

### 5.1 INCLUSION CRITERIA

All patients who present to the ED of the six participating institutions will be assessed for eligibility. The screening process will be compliant with each study site's provincial and institutional policies and legislation.

To be eligible to participate in the study, individuals must meet **all** of the following criteria:

1. Provision of signed and dated informed consent and assent (where applicable) forms
2. Stated willingness to comply with all study procedures and availability for the duration of the study.
3. Diagnosis of acute intestinal infectious process confirmed by the treating ED physician: *The diagnosis of gastroenteritis/acute intestinal infectious process is at the discretion of the emergency department supervising physician. Alternative terminologies that reflect a similar diagnosis are acceptable provided they meet all other eligibility criteria. Examples include: viral illness, diarrhea, vomiting, upper respiratory infection, post-infectious gastroenteritis, antibiotic associated diarrhea, toddlers diarrhea, viral infection, enteritis, viremia, fever, and bronchiolitis.*
4. Child/youth aged 6 months to 17.99 years.
5. Presence of ≥ 3 episodes of vomiting in the preceding 24 hour period (in the 24 hours preceding the screening process performed by the research team).
6. Duration of vomiting and/or diarrheal symptoms < 72 hours (*a 24 hour vomit and diarrhea free interval denotes a separate illness and only continuous days since the last 24 hour vomit and diarrhea free period are included*).
7. A minimum of 1 episode of vomiting within 6 hours of the screening process performed by the research team (time of approach and screening to be recorded): Date of time of assessment of eligibility for this study.
8. A minimum of 1 dose of ondansetron (oral or intravenous) provided during the current emergency department visit.

*Due to the nature of the illness being studied and the fast paced environment of the Emergency Department, preliminary screening may occur prior to obtaining a final diagnosis and/or an order for ondansetron.*

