  - b) Medications known to cause torsades de pointes (e.g. macrolide antibiotics, apo morphine (*a morphine decomposition product that does not contain morphine or it's skeleton, nor does it bind to opioid receptors; acts as an antagonist of 5-HT2 and  $\alpha$ -adrenergic receptors with high affinity*)
  - c) Medications that cause electrolyte abnormalities (e.g. high dose corticosteroids, diuretics)
  - d) Serotonergic or neuroleptic medications: *Risk of serotonin syndrome or neuroleptic malignant syndrome* (e.g. triptans, SSRIs, SNRIs, fentanyl, MAOIs, lithium)
  - e) Any 5-HT3 receptor antagonist excluding ondansetron: *Cross reactivity has been reported between different 5-HT3 antagonists*
8. Unable to complete follow-up due to travel, no telephone or internet availability, or a language barrier beyond reasonable accommodation.
9. Previously enrolled in this study.
10. History or family history (first degree relative) of G6PD deficiency: *Due to the small amount of quinine present in the placebo compound which in theory can trigger a hemolytic crisis.*

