### 5.5 STRATEGIES FOR RECRUITMENT AND RETENTION

Participants will be recruited from six EDs across Canada. Patients will be approached for permission to participate in research according to local policy and procedure. Only patients who have been administered a minimum of 1 (one) dose of ondansetron by the clinical team will be approached for participation in the study.

To ensure study retention, trained research study staff will review the study in detail with the patient and/or caregiver emphasizing the risk, benefits, and time commitment required prior to consent.

Follow up will be performed 24 and 48 hours following enrollment, as well as on Day 7 (168 hours after enrollment). Caregivers will have the opportunity to complete follow-up by email or telephone. If no response is received via email within 24 hours of the email send time, a follow-up telephone call will be performed to obtain the necessary data. If unable to make contact via telephone within the first 24 hours, 3 (three) additional attempts per follow-up time point will be made to contact the caregiver and/or participant by telephone over the subsequent 5-14 days.

There will be no financial reimbursement associated with this trial.

*For a more detailed description of recruitment and retention plans, see the TMOP and site specific SOPs.*

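### The synopsis counts the 8-hour wait before the first home dose from the initial ED ondansetron dose; if a child was re-dosed in the ED, it should count from the most recent one

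*Combined protocol and SAP*

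**What the plan says.** The synopsis (1.1, Description of Study Intervention) sets the start of home dosing: study doses are "to be administered no sooner than 8 hours after the initial clinical dose was provided by the ED physician". The same sentence admits children who had at least one ED dose in routine care.

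Other sections fix who can enter and how doses are spaced:

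- Inclusion criterion 8 (5.1) requires "A minimum of 1 dose of ondansetron (oral or intravenous) provided during the current emergency department visit", and 5.5 approaches "Only patients who have been administered a minimum of 1 (one) dose of ondansetron by the clinical team". Both set a floor and no ceiling.
- Exclusion 7e (5.2) bars any 5-HT3 "receptor antagonist excluding ondansetron", so earlier ondansetron does not exclude a child.
- Section 6.5 lets the treating physician give a participant other medicines in the ED, but not ondansetron.
- Schedule of Activities (1.3), footnote a: "First dose of study intervention can be administered 8 hours after administration of clinical dose of Ondansetron". It does not say which dose counts if there were several.
- Footnote b, on the end of dosing: "The final dose should be administered within 48 hours of first clinical dose of Ondansetron".
- Section 6.1.2 spaces home doses 8 hours apart, with at most three in 24 hours, and does not require all six to be taken.
- Section 4.3 on timing advice to caregivers: "We will have a standardized written handout that the research staff will employ explaining when we suggest that the medication be given". The handout itself is not in the documents.

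**The concern.** An 8-hour wait ought to separate the first home dose from the ondansetron the child last received. Counted from the initial ED dose, it does so only when there was a single ED dose. Section 6.5 does not close the gap: it governs children already in the study, whereas families are approached only after at least one clinical dose, so a second dose may already have been given.

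At stake is the dosing interval for some children in the active arm. A caregiver who follows the stated rule exactly could give ondansetron sooner after the last ED dose than the protocol allows between any two home doses.

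**Working it through.** **Inputs.** The minimum wait is 8 h from the initial ED dose (1.1). Home spacing is 8 h (6.1.2). The half-life is about 3 to 4 h (6.2.2). The time from first to last ED dose, t, is not given in the documents; values of 1, 2, 4 and 6 h are assumed to show the range.

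**Plan's own figure.** For a child with one ED dose, t = 0 and the gap is 8 - 0 = 8 h, as intended.

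**Gap for a re-dosed child, read literally.** Gap = 8 - t. For context, the share of the last ED dose still present after the gap is 0.5^(gap / half-life). This assumes that the dose was retained and that decay is simple and first-order.

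| t (h) | Gap (h) | Share left, half-life 3 h | Share left, half-life 4 h |
|---|---|---|---|
| 0 (one ED dose) | 8 | 0.157 | 0.250 |
| 1 | 7 | 0.198 | 0.297 |
| 2 | 6 | 0.250 | 0.354 |
| 4 | 4 | 0.397 | 0.500 |
| 6 | 2 | 0.630 | 0.707 |

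The gap is under 8 h for any t above zero. The last row needs two ED doses 6 h apart, both before enrolment.

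**If the wait runs from the most recent ED dose.** The gap is at least 8 h for every child, whatever t is.

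**Room for six doses.** Measure time from the first ED dose.

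- As written, 8-hourly doses can fall at 8, 16, 24, 32, 40 and 48 h. All six meet footnote b's 48 h.
- After the change they fall at t + 8, t + 16, ..., t + 48 h. For t = 1 to 6 h the fifth is at 41 to 46 h and fits. The sixth is at 49 to 54 h: outside footnote b's 48 h, but before the 72 h at which the same footnote calls a dose a deviation.
- Section 6.4 instead allows 48 h from ED discharge. Discharge comes at or after the last ED dose, so that window ends at t + 48 h or later and six doses still fit.

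No sample size, power or significance level depends on any of this.

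**The case against.** The strongest reply is that the authors pictured a single ED dose, so that initial only separates the clinical dose from the home doses. Several places support this. Section 2.1 frames the contrast as multiple doses against one dose followed by placebo. Section 8.2 and footnote a speak of the clinical dose in the singular. Footnote b does say first, which suggests that more than one was foreseen, but it governs the end of dosing, not the start. The innocent reading is therefore reasonable. It does not remove the point, because nothing in the documents states a last-dose rule and eligibility plainly admits a child with two doses.

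Other parts of the reply also stand. The wait is a floor, dosing is as needed, and zero doses is compliant (6.4), so a short gap also needs a caregiver who doses at the earliest moment. A repeat ED dose given because the first was vomited adds little exposure. The handout, discharge instructions or TMOP may already count from the last dose.

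A reader might go further and infer an unsafe exposure, for example by adding residual ED drug to the home dose and setting the sum against the range in 4.3. The documents do not support that. Section 4.3 says the regimen "is within the dosing range (0.13-0.26 mg/kg) that has previously been used for this indication", and that range is per dose, so it is no ceiling for a summed load. Section 4.3 also reports a minimal QTc effect for a single 8 mg dose, and 5.2 excludes children with known QT or arrhythmia risk. Section 6.2.2 reports higher peak levels in volunteers after 8-hourly repeat dosing (40 ng/mL) and after infusion (80-100 ng/mL) than after one oral dose (20-30 ng/mL), so a modest overlap of oral doses is not evidently a problem.

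**Conclusion.** The point holds as a minor wording matter in dosing safety. Taken literally, the synopsis permits a first home dose 8 - t hours after the last ED dose in a re-dosed child, which is shorter than the protocol's own spacing. It rests on two things: that some children are re-dosed before enrolment, which is allowed but whose frequency and timing are not given, and that the documents not available here do not already set a last-dose rule. No harm is shown.

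Nor should a reader infer a threat to the trial's validity. The ED doses in question precede randomisation and the same waiting rule applies in both arms, so the comparison between arms is not biased by it.

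**What to change.** In the synopsis, and in footnote a of the Schedule of Activities, state that the first home dose is given no sooner than 8 hours after the most recent ED dose of ondansetron. Have the research nurse write that earliest clock time on the discharge instructions and dose tracking form already completed under 6.2.4, and check that the handout and TMOP agree.

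The cost is two wording changes and one time entry; ED medications are already collected at enrolment (8.1). For re-dosed children the first home dose may come up to t hours later. Under footnote b that leaves room for five 8-hourly doses rather than six, while under 6.4 six still fit, and six are not required. Footnote b can stay as it is. Nothing changes for a child with one ED dose.
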